### Aerobic Function Measures

The assessment of aerobic function will be achieved through the 1 mile run/walk test protocol from the Fitnessgram Test Manual (81). The purpose of this test is to complete one mile in the fastest possible time. If the participant desires, walking may be interspersed with running; however, he/she should be encouraged to cover the distance in as short a time as possible. For the particular case of younger children, modifications should be introduced and a shorter test will be performed; 1/4 mile for 6–7 years old and 1/2 mile for 8–9 years old, using similar procedures to the original test protocol.

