## Abstract

Physical exercise has shown positive effects on symptomatology and on the reduction of comorbidities in population with autism spectrum disorder (ASD). However, there is still no consensus about the most appropriate exercise intervention model for children with ASD. The physical exercise program for children with autism (PEP-Aut) protocol designed allow us to (i) examine the multivariate associations between ASD symptoms, metabolic profile, physical activity level, physical fitness, and health-related quality of life of children with ASD; (ii) assess the effects of a 40-week exercise program on all these aspects of children with ASD. The impact of the exercise program will be assessed based on the sequence of the two phases. Phase 1 is a 12-week cross-sectional study assessing the symptomatology, metabolic profile, physical fitness and physical activity levels, socioeconomic status profile, and health-related quality of life of participants. This phase is the baseline of the following phase. Phase 2 is a 48-week intervention study with a 40-week intervention with exercise that will take place in a specialized center for children with ASD in the city of Maceió-Alagoas, Brazil. The primary outcomes will be change in the symptomatic profile and the level of physical activity of children. Secondary outcomes will be anthropometric and metabolic profiles, aerobic function, grip strength, socioeconomic status, and health-related quality of life. The study will provide critical information on the efficacy of exercise for children with ASD and help guide design and delivery of future programs.

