## Estimated Sample Size

The variable “occurrence of stereotyped behaviors” will be the primary outcome of this study. We will calculate the total sample from the power associated with the effect size and the difference of the means from the overall effect size of the results from similar studies that test the effectiveness of the PE programs in children’s stereotyped behaviors, clinically diagnosed with ASD (Cohen’s d effect size = 1.41) (45, 52, 53, 60).

To detect possible differences between the means of the primary measure with a power of 80% (*n* = 0.05), 39 children would be necessary to verify a positive effect of the PE program on the stereotyped behaviors of this population. In addition to these children, and aiming to prevent possible losses estimated as 30% characteristic from longitudinal PE programs, 12 participants will be added to the initial sample, and totally 51 individuals will be selected for the study (65).

For the Phase 1 cross-sectional study, it is possible to assess at least 145 participants from both sexes, with age ranging from 4 to 12 years, following a procedure reported in recent studies (40, 43).

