## Outcome Measures

All outcome measures will be collected two times: (a) in Phase 1 (cross-sectional study, weeks 1–12) and (b) in Phase 2 (intervention study, between weeks 13–16 and 57–60). Primary outcomes are related to the symptoms profile and the level of PA. Secondary outcomes will be the metabolic profile, the anthropometric measurements, the functional level, the handgrip strength, the socioeconomic status, and the health-related quality of life. A characteristic of this study is that some of the measurements are applied to participants families or legal representatives (Socio-economic Questionnaire, Child Health Questionnaire, SAT, and CATS), while others are applied to the participants with ASD themselves (PA level, anthropometric measures, aerobic function, hand-grip strength, and blood collection).

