## Data Analysis

The distribution patterns for each variable will be assessed by visual inspection. For convenience, when needed, transformations on the variables will be made to approximate to Gaussian distributions. A multilevel modeling framework will be used, as it is a flexible approach to deal with hierarchical data, such as repeated measures, as well as the possibility to account for different levels of variation at higher orders. Particularly, multilevel modeling allows for improved estimates with repeated sampling, improved estimation with unbalanced designs, considering and modeling different patterns of variation, avoiding averaging, and retaining variation (90). Furthermore, the multilevel modeling framework is an alternative to the well-known limitation of traditional single-level-based approaches (90–95). Inspection of variation within and between clusters (i.e., groups) will be initially explored with unconditional means models, which includes only the random parameters, to measure the proportion of the total variance, which is between-participants, particularly grouped as intervention and control groups, i.e., variance partition coefficient (92). The variance components models allow the determination of whether baseline values were clustered by intervention or control group.

To examine the responses to the exercise-based intervention program in children with ASD (dummy valuable—control group coded 0, intervention group coded 1) on dependent variables, we will assume measures (level-1 unit) nested within participants (level-2 unit). A progression of two-level growth model will be used, initially considering a random intercepts models, followed with random intercepts and slopes models. Considering both variability patterns at intercept (i.e., baseline), and at slope (i.e., response to intervention) and its covariance patterns which will allow the identification of the most parsimonious model to describe the data. In addition, time variant covariates (e.g., body mass or hormone levels) and time invariant covariates will be considered for the exploration of mediating effects of responses to the intervention. To make inferences about the true (population) values of the effect of exercise-based intervention on dependent variables, the size of the SD for individual responses will be interpreted in relation to the baseline between-participant SD (96).

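### The run/walk distance depends on age, but the plan does not say whether a child keeps the baseline distance at follow-up, and it gives no shortened distance for ages 4–5

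*Protocol article*

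**What the plan says.** The section Aerobic Function Measures describes a timed test: "The purpose of this test is to complete one mile in the fastest possible time". It says that younger children get a shorter test and gives the distances as "1/4 mile for 6–7 years old and 1/2 mile for 8–9 years old, using similar procedures to the original test protocol". By implication, one mile applies from age 10. Ages 4 and 5 have no entry.

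The section Estimated Sample Size describes the Phase 1 children as "with age ranging from 4 to 12 years". No separate range is given for Phase 2, but the Abstract says of Phase 1: "This phase is the baseline of the following phase".

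The section Outcome Measures places the Phase 2 assessments "between weeks 13–16 and 57–60". The section Data Analysis treats repeated results as belonging to the same child: "we will assume measures (level-1 unit) nested within participants (level-2 unit". The Abstract makes the outcome secondary: "Secondary outcomes will be anthropometric and metabolic profiles, aerobic function, grip strength, socioeconomic status, and health-related quality of life".

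The article does not say whether age at baseline or age at the visit decides the distance. It does not name the analysed score (time, speed or something else).

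**The concern.** A time to complete a distance has meaning only for that distance. The stated distances double at the 8th birthday (1/4 to 1/2 mile) and again at the 10th (1/2 to 1 mile), and the two Phase 2 visits are most of a year apart. If assessors apply the bands at each visit, which is the natural way to read them, a child who crosses a boundary will show a much longer time at follow-up whatever happened to fitness. In a model of within-child change, that jump is read as a response.

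The lower end of the age range raises a second problem. Read literally, children of 4–5 get the full mile while those of 6–7 get a quarter of it, which contradicts the sentence's aim of a shorter test for younger children. A child who turns 6 between visits would go from one mile to 1/4 mile, an artefact in the opposite direction.

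At stake is the precision of the only aerobic measure in a trial that lists physical fitness among its aims.

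**Working it through.** The plan gives no figure for how many children change distance, so there is none to reproduce.

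**Inputs from the article**
- Distances: 1/4 mile at 6–7, 1/2 mile at 8–9, one mile otherwise (Aerobic Function Measures).
- Visits: weeks 13–16 and 57–60 (Outcome Measures).
- Ages: 4 to 12, stated for Phase 1 (Estimated Sample Size).
- Trial size: 51 (Estimated Sample Size).

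**Assumptions**
- Phase 2 ages are uniform over the Phase 1 range. It is taken as 9 years wide if 12 includes children up to the 13th birthday, and otherwise as 8 years wide.
- Age at each visit sets the distance.

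**Interval between visits**
- Midpoints 14.5 and 58.5 weeks: 58.5 − 14.5 = 44 weeks; 44/52.18 = 0.843 years.
- Shortest: 57 − 16 = 41 weeks. Longest: 60 − 13 = 47 weeks.
- If the Phase 1 measurement (midpoint week 6.5) is the baseline: 58.5 − 6.5 = 52 weeks.

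**Share whose distance doubles.** A child crosses if baseline age lies within the interval g below 8 or below 10, so the share is 2g/width.

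| Interval | Width 9 years | Width 8 years |
|---|---|---|
| 41 weeks | 17.5% | 19.6% |
| 44 weeks | 2 × 0.843/9 = 18.7% | 2 × 0.843/8 = 21.1% |
| 47 weeks | 20.0% | 22.5% |
| 52 weeks | 22% | 25% |

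At 44 weeks this is 0.187 × 51 = 9.6 to 0.211 × 51 = 10.8 children. With truncated normal ages (means 6 to 10.5 years, SD 1.5 to 2) the share at 44 weeks runs from 16% to 34%.

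**Ages 4–5**
- At baseline: 2/9 = 22% to 2/8 = 25%.
- Turning 6 between visits: 0.843/9 = 9% to 0.843/8 = 11%.

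**Size of the artefact in one child.** Assume a pace of 14 min per mile. A child who turns 8 takes 14/4 = 3.5 min at baseline. With a true 10% reduction in time, follow-up is 0.9 × 14/2 = 6.3 min. The child has improved, but the recorded time has risen by 2.8 min.

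**Illustrative power.** The inputs are all assumed: ages 6 to under 13, 18 per arm, 14 min per mile, 20% between-child and 8% within-child variation, a true 10% reduction, and pace that does not depend on distance. In this age range about 24% cross a band (2 × 0.843/7).

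| Analysis | Distance at follow-up | Power |
|---|---|---|
| Raw time | by age at visit | 20% |
| Raw time, adjusted for change in distance | by age at visit | 63% |
| Log time, adjusted for crossing a band | by age at visit | 76% |
| Log speed | by age at visit | 77% |
| Raw time | baseline distance kept | 61% |

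The SD of change in raw time is about 2.7 min with changing distances and about 1.2 min with fixed distance. The loss therefore comes from pooling raw times over different distances. Speed recovers it in this model even when distances change.

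**The case against.** The strongest reply is that the harm needs an analysis the article never states. The test section describes how the test is run, not which variable is analysed. Data Analysis allows transformations and covariates, and the derivation of a score is commonly left to an analysis plan, which is not shown. The article also does not say that age at the visit decides the distance. The range of 4 to 12 is stated for Phase 1, and eligibility gives no ages. All of this is fair. It means that the shares above are conditional, and that the fall to 20% power illustrates one analysis and does not forecast the trial's result.

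A reader might also infer that the comparison of arms is biased. The documents do not support that. Allocation is randomised, so birthdays are balanced in expectation, and a chance imbalance among some ten crossing children is sampling error already contained in the wider SD. Nor do the documents show that children of 4–5 will give missing or invalid results. What they show is a missing band.

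What remains is more than omitted detail. The article chose numeric bands for a test repeated in the same growing children, and following them at both visits gives results that cannot be compared directly. Converting to speed repairs this fully only if pace is the same over different distances, and the article gives no ground for assuming so.

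**Conclusion.** The concern stands in a limited form. The age bands, the gap of about 44 weeks and the within-child analysis do not fit together unless the plan fixes each child's distance or uses a distance-free score, and it states neither. If age at each visit decides, about 19–21% of children (10 to 11 of 51) run twice the distance at follow-up, given uniform ages over 4–12. Other age shapes give 16–34%. The consequence is mainly added noise on a secondary outcome. The primary outcome and the sample size are unaffected.

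The gap at ages 4–5 stands on the text as an inconsistency between Estimated Sample Size and Aerobic Function Measures. How many of the randomised children it touches depends on the Phase 2 ages, which the article does not give. The point should be corrected before follow-up testing, but it does not threaten the trial's main conclusion.

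**What to change.** - State in the test procedure that each child is tested at both visits over the distance set by age at baseline.
- Analyse speed, preferably on the log scale, adjusted for baseline speed and distance band. Fixing the distance makes the two results comparable within a child. Speed with band adjustment handles comparison between children.
- Reconcile the age range with the bands: state what applies at ages 4–5, or that these children do not contribute to this outcome. The distance itself is for the investigators to decide.
- If some children have already been retested over a different distance, record the distance run at each visit, analyse log speed, and mark those children for a sensitivity analysis.

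The cost is a sentence or two and one derived variable. Children who cross a band run a shorter distance at follow-up than their age band prescribes, so their follow-up results cannot be set against age norms.

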### Hand-Grip Strength Measures

Manual gripping force (kgf) will be assessed using a SAEHAN^®^ Hydraulic Hand Model SH5001 dynamometer. The position used for the data collection is the one recommended by the Brockport Fitness Test Manual (82).

### Blood Sample and Analysis

Blood will be collected by venepuncture, in a fasting state, by an independent registered nurse and will be analyzed using a standard protocol (83) by a previously defined certified laboratory. Individual results are sent to the research leader in a printed format and without any storage of the biological material collected. Children’s parents or legal representatives will receive a copy of the individual lab test results containing individual information about the child’s metabolic profile (glucose, total cholesterol, triglycerides, HDL, and LDL).

## Characterization of the Physical Exercise Program (PEP-Aut)

Based on a preliminary pilot study (see Supplementary Material), the design of PEP-Aut was build and tested following recommendations from summaries of the existing literature where exercise has been used with children with ASD (22, 48, 84). In addition, we used other relevant guidelines for exercise intervention programs in the general pediatric population (85).

### Adaptation (4 Weeks)

The purpose of this phase is to enable children with ASD to adjust their behavior to the characteristics of the different exercises and tasks included in PEP-Aut (see Table 1). Adaptive sessions will be mediated by parents or legal representatives and supervised by the researcher.

**Table 1 T1:** Overview of the PEP-Aut specific physical exercises used for intervention.

Exercise	Physical ability	Description	Resource
Climbing and support in the bar	Upper limb strength	The child should climb a vertical backrest, reach the last bar, and hold the body suspended for 5.0 s	One standard vertical backrest with 1.5 m height, fixed at 0.5 m of the ground
Release to the basketball	Upper limb strength	Starting from an initial position with a mini medicinal ball close to the chest, the child should perform a shoulder lift (180°) followed by an elbow flexion, positioning the mini ball over the head. From this position, the child should then do a full extension of the upper limbs (elbow and forearm) followed by a slight flexion of the wrist, performing the ball throwing movement	One basketball table (fixed at 1.75 m from the floor), three benches to support the throwing with different dimensions (base 0.5 cm × height 0.5, 1.0, and 1.5 m); Mini medicinal balls with different weights (0.5, 1.0, and 2.0 kg)
Elastic bands workout	Upper and lower limbs strength	The child in an upright position, with the arms suspended along the body, picks up the elastic bands, which should be fixed to the floor by a safety beam, by the fists. The child should perform a simultaneous flexion of the forearms, bringing the hands closer to the shoulders for each repetition	Elastic bands
Climbing the steps and walking on the inclined plane	Lower limbs strength and coordination	The child should climb the three steps and walk on the inclined plane (hip and knee flexion movement)	l-shaped wooden staircase with three steps (0.12 m × 0.15 m) and inclined plane of 0.78 m length and 0.30 m height with handrail throughout the entire length
Step box with target	Lower limbs strength and coordination	The child should climb three sets of sequenced steps. When reaching the last step, he/she should perform a plantar flexion of the ankle and try to reach the target fixed to the wall above his/her head and score points	Six steps with the dimension of 0.60 m × 0.28 m × 0.14 m overlapped and placed in ladder. The first step consists of a unique step, the second step consists of two sets of overlapping steps, and the third step consists of a set of three overlapping steps, respectively
Sequenced march	Coordination	The child should perform front running on a sequence of five arcs arranged sequentially in the ground	Five plastic bows with 0.50 m in diameter

### Intervention (40 Weeks)

After the adaptation to the exercises, the PEP-Aut sessions will have the following structure:
(a)Preparatory phase (5 min)—Time period where ASD children are prepared for the exercise session, including active search, displacement of the children and their parents/legal guardians to the transition area, placement of the heart rate monitor and of the leg and ankle weights, and transfer of the child to the PEP-Aut working area (indoor or outdoor).(b)Development phase (30 min)—Time period where children perform a brief warm up and perform strength, balance, and coordination exercises in a training environment. The sequence of the exercises in the program is not rigid to maintain high levels of interest and fun. Different motivational strategies were used to maintain motivation and adherence to the PEP-Aut including using different materials, different colors, music in some sessions, and small rewards. Such strategies may contribute to reduce or eliminate barriers during the sessions influencing the participation and permanence of the child in the sessions.

The equipment needed to implement the PEP-Aut sessions will be presented simultaneously in the working space using a circular organization. The type of communication employed with each child will be determined in consultation with parents/legal representatives. We will adopt three levels of mediation: (a) oral explanation of the exercise facing the child, (b) oral explanation with subsequent modeling, and (c) oral explanation, modeling, and child orientation throughout the intervention process (skills development and acquisition).

(c)Return to calm phase (5 min)—After the development phase, the child should move to the transition area, remove the leg and ankle weights, and start immediately the relaxation activities. Parents and legal representatives will perform relaxation exercises using tactile slip skills on the child’s back and belly aiming to return the child to calm. These procedures will respect the child’s choice about his/her favorite position for the relaxation massage: (a) laying on the mat, (b) in a sitting position on the mat, or (c) standing still on the mat.

## Description of PEP-Aut Exercises

According to the review of literature, manipulative strength, balance, and coordination are physical qualities that are often impaired in children with ASD (22, 48). Such interference is due to its relation with stereotyped movements that may appear in different ways.

The most frequently mentioned in the literature are the movement of the hands, the nods or shaking of the arms, sudden runs, body swing backward and forward, repeated manipulation of objects and fingers movements (32). These type of movements present a direct relationship with the type of exercises selected for the PEP-Aut (see Table 1).

## Adaptations of the PEP-Aut Setting

Selecting the most appropriate environment to develop an intervention project with PE requires a previous diagnosis to identify which open and closed physical space are more likely to reduce the ASD children’s level of stress. Children with ASD are less tolerant to routine changes and are resistant to new activities. For the protocol of this study, we decided to describe not only the adaptation procedures related to the physical space used during the adaptation phase of the pilot study but also those used to form the groups and to determine the type of mediation to be used.

### Physical Space

First and second sessions will be held indoor, in a global area of 40 m^2^ divided into three fixed areas, one with 2 m^2^ as a transition area, another with 36 m^2^ as a working area, and a third of 2 m^2^ as a relaxation area. The following sessions will be held in open space in an area with similar dimensions. The results of the adaptive phase of the pilot study will allow the identification of the most adequate physical space to implement PEP-Aut, for each child, and assess the possibility to use one or two types of physical space to implement the program.

### Group Environment

PEP-Aut sessions should probably function with ASD children in pairs or trios, escorted by the parents/legal representatives with the aim of building a positive motivational and socialization environment and reducing the symptoms of the disorder. Thus, the identification of each pair or trio will depend on (a) individual analysis of the child’s symptom profile based on “social interaction difficulty,” “hyperactivity/hypoactivity,” and “inappropriate reactions to frustration” variables so that pairs and trios with compatible profiles can be identified; (b) assessment of partnerships between children in both indoor and outdoor environments, with the help of parents/legal representatives; (c) not using rigid group composition, safeguarding the identification of future unproductive partnerships; and (d) children exhibiting tantrum, self- and hetero-aggression behavior, and shouting and rejection during adaptive sessions will start their PEP-Aut sessions individually and be assessed regularly about the possibility of inclusion in pairs or trios.

